### 2.5. Procedure and Data Collection

We will collect general structural data (see Figure 1) for each participating study center. All patients treated in the participating ICUs in a 14-day period will be included. Notably, only data generated in the context of standard patient care will be collected. For each patient treated in the participating ICUs, the following data will be collected: gender, age, date and time of hospital admission, referring ward or hospital (if applicable), Simplified Acute Physiology Score (SAPS) II, date and time of hospital discharge, patient status at discharge (alive, dead, returning home, or going to a care facility). In addition, for each patient we intend to collect data describing the dates and times of ICU admission and discharge as well as the type of admission (surgery—planned or emergency; medical treatment—planned or emergency) and the survival status at ICU discharge.

For each patient diagnosed with sepsis or septic shock during the observation period, more detailed information will be collected (date and time of sepsis onset, date and time of septic shock onset, infectious focus, causative pathogen(s), and secondary infections (super- and/or nosocomial infections and/or infections of a further organ system)). Furthermore, investigators will be asked to extract data from the hospital information system describing additional patient characteristics. These include the American Society of Anesthesiologists (ASA) classification [16], the Revised Cardiac Risk Index (RCRI) [17] score, the status of and, if applicable, the reason for pre-existing anticoagulation therapy or antiplatelet therapy, coagulopathy, and severe liver disease. Furthermore, information on past episodes of heparin-induced thrombocytopenia (HIT) type II will be collected. For all patients hospitalized with sepsis in the ICU on the first day of the observation period, it will be determined whether SIC was present before the start of the observation period. Furthermore, for each patient diagnosed with sepsis or septic shock during the observation period, on the day of sepsis diagnosis (day 0), on days 1–4, and on the day of sepsis discharge, the following measures will be collected: the sequential sepsis-related organ failure assessment (SOFA) score [2], the international normalized ratio (INR), and platelet count. For further exploratory analyses, the following parameters are recorded where available: anti-factor Xa activity, activated partial thromboplastin time (aPTT), prothrombin time, D-dimer level, fibrinogen concentration, thrombin–antithrombin complex (TAT) concentration, thrombin fragment F1.2 concentration, and measures from thrombelastometric testing. Likewise for exploratory analyses, the following parameters are collected: the levels of inflammation markers (C-reactive protein (CRP), procalcitonin (PCT), and interleukin-(IL) 6), as well as the dose of anticoagulant administered, the amount of fluid infused (per day), the amount of blood products transfused (per day), and the administered amount of coagulation factors and desmopressin (per day), determined at the same time points. Using the collected data and the SIC scores, all patients with sepsis will be tested for SIC at least once a day. Additionally, SIC scores (exact scores) will be recorded daily until day 14 after sepsis onset or discharge from the ICU (whatever occurs first). The date and time of the first SIC occurrence will be registered. The data collected will also be used to calculate the severity of SAC, according to Lyons et al. [6]. Finally, until day 14 after the onset of sepsis, each patient will be checked for thromboembolic events and non-trauma or surgery-related major bleeding (causing a drop in hemoglobin of <1 g/dL) once a day. In addition, on the 28th day after sepsis onset, it will be determined whether cardiovascular events, thromboembolic events, or non-trauma or surgery-related major bleeding (causing a drop in hemoglobin of <1 g/dL) occurred during the second 14 days of follow-up monitoring (yes/no recording for the second 14 days). Figure 2 provides an overview of the planned timeline. The time frames were chosen on the basis of balancing efforts and benefits. Since it is currently assumed that SIC occurs in the early phase of sepsis due to a dysregulation of the interaction of the innate immune response with the coagulation system, a special focus was placed on the first days, i.e., day 0 (sepsis onset) and the following 4 days. The aim is to identify possible early warning signs of SIC. Sepsis is usually treated anti-infectively for 7–14 days. The first occurrence of SIC after day 14 was considered very unlikely. The experts involved in the study planning were of the opinion that the occurrence of SIC after day 14 was most likely due to a secondary infection (which triggers a new sepsis episode) or another sepsis-independent reason. It was decided to use the 28-day mortality rate, as it is frequently collected in sepsis studies and thus allows an approximate comparison of the mortality of this cohort with other study cohorts. In the aforementioned effort to balance efforts and benefits, it was decided to investigate the potential effects of SIC on thromboembolism and bleeding risk up to day 28.

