### 2.4. Outcomes

The primary outcome parameters of the INSIC trial are as follows:
(1)The incidence rate of SIC within a 14-day observation period (new cases/1000 patient days).(2)The point prevalence of SIC on day 1 of the study period and on three reference days in the 4th quarter of each year from 2019 to 2023.

The secondary outcome parameters of the INSIC trial are as follows:
(1)Length of stay in the ICU until transfer to a normal ward.(2)ICU mortality rate (in all patients and in the subgroups of patients with sepsis, septic shock, SIC, or SAC (mild, moderate, severe) according to the different scores).(3)Mortality rate until day 28, hospital death, or hospital discharge (whatever occurs first, in all patients and in the subgroups of patients with sepsis, septic shock, SIC, or SAC (mild, moderate, severe) according to the different scores).(4)SIC and SAC (mild, moderate, severe) recovery rate 72 h after SIC or SAC onset. The time point was chosen as the 72 h period reflects a critical window during which early death in sepsis or a clinical response to sepsis therapy can be expected [15].(5)Thromboembolic events after sepsis onset (in sepsis, septic shock, SIC, or SAC (mild, moderate, severe)) up to day 28, death, or hospital discharge (whichever occurs first).(6)Relevant bleeding without surgical trauma (hemoglobin loss >1 g/dL within 24 h, due to bleeding rather than dilution) after sepsis onset (in sepsis, septic shock, SIC, or SAC (mild, moderate, severe)) until day 28, death, or hospital discharge (whichever occurs first).

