**Figure 2 jcm-14-04222-f002:**
[figure not shown]
Overview of the timeline of the INSIC trial. SIC = sepsis-induced coagulopathy.

**Table 1 jcm-14-04222-t001:** Sepsis-induced and sepsis-associated coagulopathy scores.

SIC Score Iba et al. [4]			SAC Score Lyons et al. [6]
		Points	
Platelet count SIC subscore (PSSC) (platelet count (PLC) [1/nL]	>150/nL	0	**Mild SAC** 1.2 ≤ INR < 1.4 **and** 100 > PLC ≤ 150
	100 to <150/nL	1	
	<100/nL	2	
International Normalized Ratio (INR) SIC subscore (ISSC) [ ]		0	
	≥1.2 to <1.4	1	
	≥1.4	2	
SOFA subscore (truncated SOFA score, including the respiratory, cardiocirculatory, hepatic, and renal subscore) [Points]	0	0	
	1	1	
	≥2	2	**Moderate SAC:** 1.4 ≤ INR < 1.6 **or** 80 ≥ PLC ≤ 100;
No SIC		<4 points	**Severe SAC** INR ≥ 1.6 **or** PLC < 80
SIC		≥4 points (with PT-INR plus platelet count exceeding 2)	

ISSC = international normalized ratio (INR) SIC subscore; PLC = platelet count; PSSC = platelet sepsis-induced coagulopathy subscore; SAC = sepsis-associated coagulopathy; SIC = sepsis-induced coagulopathy; SOFA = sequential (sepsis-related) organ failure assessment.

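### Graded 72-hour SAC recovery has no limit on onset day, but the INR and platelet values it needs are scheduled only for days 0–4 and discharge

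*Protocol article*

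**What the plan says.** Section 2.4, secondary outcome (4), is the "SIC and SAC (mild, moderate, severe) recovery rate 72 h after SIC or SAC onset". No onset window is attached to it.

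Section 2.5 sets three recording schedules:

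- SOFA, INR and platelet count are recorded "on the day of sepsis diagnosis (day 0), on days 1–4, and on the day of sepsis discharge, the following measures will be collected".
- Products are listed for exploratory analyses: "the amount of blood products transfused (per day), and the administered amount of coagulation factors and desmopressin (per day), determined at the same time points".
- For SIC itself, "SIC scores (exact scores) will be recorded daily until day 14 after sepsis onset or discharge from the ICU (whatever occurs first"). Patients with sepsis are also tested for SIC at least once a day, and the date and time of first SIC are registered.

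No separate daily SAC recording is stated. Instead, "The data collected will also be used to calculate the severity of SAC".

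Table 1 gives the cut-offs. SIC points stop at INR ≥1.4 and platelets <100/nL (2 points each). SAC adds a severe grade at INR ≥1.6 or platelets <80/nL.

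**The concern.** A SAC grade needs the actual INR and platelet count. The outcome asks for a status three days after onset, whenever onset occurs, while the scheduled raw values stop at day 4 apart from the discharge day. Section 2.5 calls a first SIC very unlikely only after day 14, so the plan itself expects that coagulopathy may begin well after day 1.

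At stake is how far the study can describe the course of SAC by severity. That matters because the Introduction motivates the study with a failed trial in which about 20% of patients had remission of SAC, not SIC, before the first dose of study drug. Products shift INR and platelets directly, so a reader planning a trial will also want to know how much of the observed recovery followed platelets, plasma or coagulation factors.

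**Working it through.** The plan states no figure to reproduce. The check sets the schedule against the endpoint, then asks what the daily SIC score can replace.

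**Step 1: schedule.** Take 72 h as three calendar days, so onset on day d is assessed on day d + 3. Scheduled raw values and products: days 0, 1, 2, 3, 4 (discharge day aside). SIC score: to day 14 while the patient stays in the ICU.

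| Onset day | 72-h day | Raw INR and platelets at onset | Raw INR and platelets at 72 h | Product days missing, of the 4 from d to d + 3 | SIC score at 72 h |
|---|---|---|---|---|---|
| 0 | 3 | yes | yes | 0 | yes |
| 1 | 4 | yes | yes | 0 | yes |
| 2 | 5 | yes | no | 1 | yes |
| 3 | 6 | yes | no | 2 | yes |
| 4 | 7 | yes | no | 3 | yes |
| 5–11 | 8–14 | no | no | 4 | yes |
| 12–14 | 15–17 | no | no | 4 | no |

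So 72-h SIC recovery is computable for onset days 0–11 (11 + 3 = 14), and 72-h graded SAC for onset days 0–1 (1 + 3 = 4).

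**Step 2: any SAC from the SIC total.** Let c = INR points + platelet points (0–4) and s = SOFA points (0–2), so the total is T = c + s. From Table 1, mild SAC is 1 + 1, and moderate or severe SAC has at least one 2. Hence any SAC is equivalent to c ≥ 2.

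- T ≥ 4: c ≥ 4 − 2 = 2, so some SAC is present.
- T ≤ 1: c ≤ 1, so no SAC.
- T = 2: (s, c) = (0, 2) is SAC; (1, 1) and (2, 0) are not.
- T = 3: (0, 3) and (1, 2) are SAC; (2, 1) is not.

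Totals of 2 and 3 are therefore ambiguous unless the SOFA points are known, and SOFA is on the same days 0–4 list. If s = 2, both totals mean no SAC.

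**Step 3: the grade from the SIC score.** T = 4 fits mild, moderate or severe; T = 5 or 6 fits moderate or severe. Even with subscores kept, only none (c ≤ 1) and mild (1 + 1) are identified. INR 1.5 and INR 1.8 both score 2, as do platelets of 90 and 60/nL, so moderate and severe stay merged.

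**Step 4: SIC status at a total of 4.** SIC requires "≥4 points (with PT-INR plus platelet count exceeding 2"), that is T ≥ 4 and c > 2. In the order (SOFA, INR, platelets), the patterns (0,2,2), (1,1,2) and (1,2,1) are SIC; (2,0,2), (2,1,1) and (2,2,0) are not. The total alone does not allow a central check of SIC status, but the plan does not rely on the total alone, since SIC is tested daily at the site.

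**The case against.** The strongest defence is that the daily SIC score supplies most of what recovery needs. If recovery means that SAC has resolved, the 72-h value need only be present or absent. For onset on days 2–4 the onset grade comes from raw values, and T ≥ 4 or T ≤ 1 settles the 72-h status. This stands. It leaves totals of 2–3, any step-down from one grade to another, and the grade at onset after day 4.

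A reader might go further and infer that SAC recovery cannot be computed at all for onset after day 1, or that later SAC goes undetected. Step 2 shows otherwise: a total of 4 or more reveals it, and discharge-day values exist.

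A reader might also infer that spontaneous SIC recovery cannot be verified. The documents do not support that either. The Abstract uses the term for recovery under standard treatment and sets no product-free condition. For onset on days 0–1, products are recorded throughout the window. Nor does a total of 4 leave SIC status unknown, because status is tested daily and nothing says that the eCRF keeps only the total.

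The early focus is also a reasoned choice: sections 2.5 and 2.7 cite workload and the absence of case fees. But the reason given for days 0–4 is finding early warning signs of SIC. It does not address an outcome read three days after an onset of any date.

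**Conclusion.** The point holds in a limited form. The graded 72-h SAC outcome can be derived from scheduled raw values only for onset on days 0–1. From onset day 2 the 72-h grade is missing unless that day is the discharge day, and relying on that exception would select patients by their course. After day 4 a new SAC cannot be fully graded. SIC recovery at 72 h remains computable for onset through day 11 while the patient is in the ICU. For onset from day 2, however, the influence of products on it cannot be fully examined, because one to four of the four window days lack product data.

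This affects one secondary outcome. Neither primary outcome, SIC incidence or SIC prevalence, depends on it.

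The number of patients cannot be computed. The article gives no distribution of onset days, and its forecast of 250–500 patients concerns SIC, not SAC.

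Assumptions: 72 h equals three calendar days; the discharge entry is a single day; the garbled SAC platelet ranges in Table 1 read 100–150/nL and 80–100/nL, leaving aside values exactly on a boundary.

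**What to change.** On every day the SIC score is recorded (to day 14 or ICU discharge), also store the INR, the platelet count, the SIC subscores and a yes/no entry for platelets, plasma or coagulation factors. Derive SIC and SAC centrally from these. Report 72-h recovery overall, and add a sensitivity analysis limited to patients without such products since onset.

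The cost is slightly more data entry: sites must already look up INR and platelets to score SIC, and only the product field is a new look-up.

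Timing may rule this out. Section 3.1.1 says recruitment started in March 2025, and section 2.18 says the data sets are irreversibly anonymised after the 28-day follow-up. If the fields can no longer be added, restrict graded SAC recovery explicitly to onset on days 0–1. The cost is then a narrower SAC outcome. For later onset, only any-SAC status could be reported, with totals of 2–3 declared indeterminate where the SOFA points are not available.

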## Abstract

**Background/Objectives:** Sepsis and septic shock are the most severe forms of infection. Due to the intensive cross-talk of the coagulation and immune system, coagulopathies regularly occur in sepsis. The International Society on Thrombosis and Hemostasis refers to these coagulation abnormalities as sepsis-induced coagulopathies (SICs). The presence of SICs can be assessed using the SIC score. In parallel, a score for “sepsis-associated coagulopathy” (SAC) was introduced that, in contrast to the SIC score, allows coagulopathy to be classified according to its severity. In the past, multicenter, randomized controlled trials have repeatedly failed to prove the efficacy of specific therapeutic measures targeting SICs or SACs. This could potentially be explained by insufficient knowledge about the prevalence and incidence of SIC and the rate of spontaneous recovery. The Incidence of Sepsis-Induced Coagulopathy (INSIC) trial is intended to address this problem. **Methods:** The aim of the INSIC trial is to measure the incidence and prevalence of SIC—in addition to the rate of spontaneous SIC recoveries—during the first days of sepsis treatment to provide a solid base of data for future interventional trials. We aim to include all patients with sepsis treated in any one of 150 participating intensive care units in 100 hospitals located in Austria, Luxembourg, and Germany to determine the prevalence of SIC (on day 1 of the study period as well as on three selected days in the fourth quarter of each year from 2019 to 2024). SIC incidence will be assessed over a 14-day period starting on 10 March 2025. Secondary endpoints are 28-day survival and the occurrence of severe thromboembolic events and bleeding. In addition, each of the aforementioned outcome parameters will be assessed for correlation with the severity classification of the SAC score. **Conclusions:** The INSIC trial is the first study to determine the prevalence as well as the incidence of SIC, to prospectively examine the course of SIC longitudinally over a 14-day period, and to determine the rate of spontaneous recoveries within 72 h under standard treatment in a large cohort of patients. This information will provide a sound basis for future studies.

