### 1.1. Objectives

The primary outcome of the INSIC trial is the SIC incidence rate within a 14-day observation period (new cases/1000 ICU days). Moreover, we aim to determine the point prevalence of SIC on day 1 of the study period and on three reference days in the fourth quarter of each year from 2019 to 2023. The secondary outcome parameters are as follows: (I) length of stay in intensive care unit (ICU) until transfer to a normal ward; (II) ICU mortality rate (in all patients and in subgroups of patients with sepsis, septic shock, and SIC according to the different scores); (III) 28-day hospital mortality rate (in all patients and in subgroups of patients with sepsis, septic shock, and SIC according to the different scores); (IV) SIC recovery rate 72 h after SIC onset; (V) thromboembolic events after sepsis onset (in sepsis, septic shock, or SIC) up to day 28, death, or hospital discharge (whichever occurs first); and (VI) relevant bleeding without surgical trauma (non-trauma or surgery-related major bleeding causing a drop in hemoglobin of <1 g/dL) after the onset of sepsis (in sepsis, septic shock, or SIC) until day 28, death, or hospital discharge (whichever occurs first). (VII) Each of the above-mentioned outcome parameters will also be tested for correlation with the different degrees of severity of SAC (according to the SAC score) (Table 1), which allows for a more differentiated assessment of the severity of coagulopathy.

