### 2.11. Data Monitoring

To enable standardized data collection across all centers, the investigators are trained via video conferencing before the start of the study. In addition, written material and a frequently asked questions (FAQ) list are available for all investigators. Furthermore, regular video conferences are offered during the ongoing study to answer questions about the study process and data collection. The FAQ list will be updated regularly. Moreover, the RedCap database used automatically checks data plausibility (according to tables of plausible values stored in advance) and completeness. Automated queries and notes are issued to the user. However, as only data collected as part of standard patient care may be entered, queries due to missing data may be ignored by the investigators. Moreover, central monitoring is carried out by the staff of IMISE Leipzig. In the event of anomalies that indicate, e.g., systematic errors in data entry, the relevant study center is contacted. As this is a trial that is purely observational in nature, no professional monitoring is planned. All local investigators are invited to keep in close contact with the principal investigator (email, telephone, video call apps) to ensure that the trial is conducted according to the protocol and regulatory requirements. Based on the experience of the INSEP study, which used a very similar study protocol and was conducted to a large extent at the same study centers by the same people, a high compliance rate regarding data collection across participating study centers is expected [18].

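### The secondary bleeding outcome is defined in contradictory ways: hemoglobin loss above 1 g/dL within 24 h in the outcome list, a drop below 1 g/dL in the objectives and the collection rule

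*Protocol article*

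**What the plan says.** The protocol article defines the bleeding event four times.

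- Section 1.1, objective VI: "non-trauma or surgery-related major bleeding causing a drop in hemoglobin of <1 g/dL". The item opens by naming the event as relevant bleeding that excludes surgical trauma, then gives this definition in brackets.
- Section 2.4, secondary outcome 6: "Relevant bleeding without surgical trauma (hemoglobin loss >1 g/dL within 24 h, due to bleeding rather than dilution".
- Section 2.5, check made each day up to day 14 after sepsis onset: "non-trauma or surgery-related major bleeding (causing a drop in hemoglobin of <1 g/dL) once a day".
- Section 2.5, single yes/no check on day 28: whether "non-trauma or surgery-related major bleeding (causing a drop in hemoglobin of <1 g/dL) occurred during the second 14 days of follow-up monitoring".

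The Abstract places bleeding among the secondary endpoints: "Secondary endpoints are 28-day survival and the occurrence of severe thromboembolic events and bleeding". Sections 1.1 and 2.4 ask for it in sepsis, septic shock and SIC, and Section 2.4 adds the SAC grades. Section 2.11 says that "written material and a frequently asked questions (FAQ) list are available for all investigators", but the content of that material is not part of the article.

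**The concern.** The outcome list sets a lower limit on the hemoglobin loss. The objectives and both collection instructions set an upper limit at the same value. Section 2.5 is where the article says what sites are to check, so the contradiction lies between what is collected and what is to be analyzed.

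At stake is the bleeding frequency in sepsis, septic shock, SIC and SAC, and every comparison between those groups. The study is meant to inform later trials that modulate coagulation, and a background bleeding rate is relevant to them. If some sites apply one rule and some the other, the pooled frequency mixes incompatible events. Differences between groups could then partly reflect which sites contributed the patients.

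**Working it through.** No sample size, power or error rate depends on this point, and the article states no bleeding rate to reproduce. The check is a comparison of the definitions.

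**Step 1. Criteria side by side.**

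| Criterion | 1.1 (VI) | 2.4 (6) | 2.5 daily check | 2.5 day-28 check |
|---|---|---|---|---|
| Hemoglobin drop d, g/dL | d < 1 | d > 1 | d < 1 | d < 1 |
| Time window for the drop | none | 24 h | none stated | none stated |
| Dilution excluded | no | yes | no | no |
| Exclusion | surgical trauma; trauma or surgery | surgical trauma only | trauma or surgery | trauma or surgery |
| Label | relevant and major | relevant | major | major |

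The daily check fixes how often sites look, not the interval over which the drop is measured.

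**Step 2. Literal reading.** Sections 1.1 and 2.5 admit {d < 1}; Section 2.4 admits {d > 1}. The intersection is empty, and d = 1 belongs to neither. An event admitted by the collection rule therefore cannot meet the outcome threshold, and an event that meets the outcome threshold is not admitted by the collection rule.

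**Step 3. Reading with the sign corrected.** Suppose Sections 1.1 and 2.5 meant d > 1. Three groups of events are still classified differently:

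- a drop above 1 g/dL that builds up over more than 24 h counts under Section 2.5 and not under Section 2.4. This matters most at day 28, where one answer covers 14 days;
- a drop above 1 g/dL in a patient who bled, but explained partly by dilution, is addressed only in Section 2.4;
- bleeding after non-surgical trauma is not excluded by the wording of Section 2.4, but is excluded in Sections 1.1 and 2.5. The phrase in those sections can also be misread as including surgery-related bleeding.

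Correcting the sign alone does not produce one definition.

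**Step 4. Could the analysis repair it?** Hemoglobin is not among the laboratory values listed for collection in Section 2.5. Transfused blood products are listed for day 0, days 1–4 and the discharge day. On the data listed, the outcome rests on the site's own yes or no and cannot be recomputed centrally. Section 2.11 plans automated plausibility and completeness checks, central monitoring for anomalies and no professional monitoring. Plausibility and completeness checks would not show which definition a site had applied.

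**Step 5. Time left to correct.** Section 2.18 says the data sets are fully anonymized after the 28-day follow-up. The Abstract gives a 14-day period from 10 March 2025, which ends on 23 March. Day 28 after a sepsis onset on 23 March is 20 April 2025 (8 days to 31 March, plus 20). This assumes that all sites kept to those dates.

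**Step 6. Who is affected.** Section 2.7 expects about 850 patients with sepsis or septic shock (approximate 95% interval 800–900). That is the number of patients checked, not a number of bleeds.

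**The case against.** The strongest reply is that this is a sign slip that no ICU physician would follow. The event is called major bleeding, which does not fit an upper limit of 1 g/dL, and three repeats are what copied wording would produce. Sites enter data in an eCRF after video training, with written material, an FAQ list and regular video conferences. None of that is shown, and the article condenses a longer protocol. The primary outcomes are not involved, and the stated basis for future trials is SIC incidence and spontaneous recovery.

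Most of this stands. A slip is the likely explanation, and the reply rules out the stronger inference that a reader might draw: that sites are recording the wrong events and that the bleeding data are unusable. The documents do not show that the smaller-than wording reached any site instrument. Nor is it an effect size to say that every event under one rule fails the other; that is only the logic of two disjoint ranges.

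The reply does not remove the contradiction. The text is current, no section reconciles the definitions, and a reader who silently corrects the sign still faces different rules on window, dilution and exclusion.

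**Conclusion.** The point holds as an internal contradiction in the definition of a named secondary outcome. The literal thresholds do not overlap; with the sign corrected, three further criteria still differ. The primary SIC incidence and prevalence outcomes are not affected.

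The size of any bias is unknown. It depends on the eCRF and FAQ wording, on how sites read it, and on a bleeding rate that the article does not give. Mis-recording is a risk, not a finding. The article does not say which definition governs. Treating Section 2.4 as the base is a judgement: it is the formal outcome list, the most complete version on timing and dilution, and its direction fits the idea of a major bleed.

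**What to change.** 1. Write one definition and use it in Section 1.1 (VI), Section 2.4 (6) and both places in Section 2.5. It should settle the direction of the inequality, the time window, the handling of dilution and the trauma or surgery exclusion. Section 2.4 is the natural base, but its exclusion must be decided rather than assumed, because it names only surgical trauma. State also what happens at exactly 1 g/dL and how the window applies to the day-28 question.
2. Check the eCRF label, the written material and the FAQ against that text.
3. If the eCRF carried the smaller-than wording, re-check positive and negative bleeding entries. Under the literal rule, a larger bleed would have been entered as no event, so reviewing only the positives would miss it. This is possible only while records can be linked to patients, before the anonymization in Section 2.18.
4. If that time has passed, report which wording sites used and state the limitation with the bleeding results.

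Cost: a wording correction in the protocol and, where needed, in the eCRF and FAQ. Site work to return to patient records arises only if the eCRF carried the smaller-than wording.
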